Therefore, the protocol proposed in this study presents different modalities of intervention in aquatic physiotherapy, this being a single session, considering low, medium, and high-intensity strategies, seeking to evaluate its effects on the biochemical and functional behavior of patients with knee osteoarthritis. It aims to identify possible variations in the concentration of the MMP-3 subfamily and the oxidative stress marker Glutathione Peroxidase (GPx) in peripheral blood, assess pain, edema, and flexibility in patients with knee osteoarthritis and in response to different aquatic physiotherapy interventions. Therefore, understanding the appropriate exercise intensity, coupled with understanding its effects on biochemical mediators directly involved in the genesis of osteoarthritis, can provide confidence for the prescription and execution of therapeutic exercises under immersion in aquatic physiotherapy treatment. These strategies may increase treatment adherence, prevent symptom exacerbation, minimize adverse effects, and provide greater therapeutic safety.

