## Methods

### Trial design

This is an interventional transversal study, randomized clinical trial, crossover type with three arms: low, medium, and high-intensity aquatic physiotherapy.

This clinical intervention protocol follows the recommendation from the Standard Protocol Items: Recommendations for Interventional Trials (SPIRIT).
^
31
^
^,^
^
32
^ The study sample, defined according to criteria, will be submitted to a single session of each one of the following modalities of aquatic physiotherapy: (a) low-intensity, (b) medium-intensity, and (c) high-intensity. Among each modality, a minimum of a 15-day wash-out period will be respected, in accordance with
Figure 1.

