### Outcomes

Initially, all participants will be interviewed and evaluated in relation to the degree of osteoarthritis and functionality. Information regarding the patient data will be confirmed
*via* interview, considering data such as complete name, date of birth, age, affected knee(s), duration of pain, arterial blood pressure, list of medications in use, consumption of tobacco or alcohol, associated diseases, if they are undergoing physiotherapy treatment or regular physical activity.

The classification regarding the degree of osteoarthritis will be performed by analyzing the radiograph of the affected knee according to the method of Kellgren and Lawrence. The radiographs will be analyzed, the degree of osteoarthritis will be identified with the negatoscope support, and the images in the digital form will be displayed on a computer screen, considering the classification expressed in degrees ranging from zero to IV.

Subsequently, the identification of functionality will be assessed according to the Brazilian version of the Knee Injury and Osteoarthritis Outcome Score (KOOS). The KOOS questionnaire was developed in the 1990s as an instrument to evaluate the patient’s perception of their knee and associated problems. Since its first publication in 1998, the psychometric properties of KOOS were evaluated in a systemic review of 37 articles demonstrating adequate validity in its use for the study population.
^
37
^

Regarding the pre- and post-intervention assessment instruments, all participants will have the following parameters evaluated: concentration of MMP-3 and GPx, pain, edema, flexibility, and self-perception of the general well-being. In addition, it should be noted that in the 24-hour-follow-up, only the biochemical concentrations and the self-perception questionnaire will be reevaluated.

The biochemical variables will be measured in peripheral blood from the concentrations of MMP-3 and GPx. The levels of MMPs will be measured based on the Enzyme-Linked Immunosorbent Assay (ELISA) methodology, which is based on the antigen-antibody interaction and will be performed according to the kit manufacturer’s instructions. MMP-3, a constituent of the stromelysin family that is an important mediator responsible for the degradation of collagen type II, IX, and XI,
^
12
^
^,^
^
13

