### Monitoring

*Data monitoring*

We perceive the establishment of a Data Monitoring Committee as unnecessary due to the brief duration of this study and the established safety levels associated with aquatic physiotherapy for patients diagnosed with knee osteoarthritis.

*Harms*

In our study, an adverse event will be defined as any unfavorable functional occurrence in an individual consistently linked to exercise intensity. Adverse events will be documented after the subject provides consent and enrollment in the study. Researchers will evaluate the connection between an event and the exercise intensity of the study protocol, based on a temporal relationship, in addition to assessing whether the event is unexpected or unexplained. The study will meticulously track the subsequent protocol-associated adverse effects: heightened pain, inflammation, and diminished flexibility immediately post-intervention and at the 24-hour mark through patient examination. For any circumstance that may necessitate urgent medical support, the emergency medical service of the Aquatic Physiotherapy department will be activated to ensure the requisite and appropriate assistance.

*Auditing*

Regarding this matter, we find it unnecessary due to the nature of our single-center study, which involves a limited sample size and employs a therapeutic approach that has been well-established as safe.

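### Scheduled looks for the named harms stop at 24 hours while sessions are at least 15 days apart, so later flares are not described as actively sought and may be under-counted

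*Protocol article*

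**What the plan says.** The Harms paragraph of the Monitoring section sets two looks for the effects it names: "heightened pain, inflammation, and diminished flexibility immediately post-intervention and at the 24-hour mark through patient examination". The same paragraph opens general recording at enrollment, "Adverse events will be documented after the subject provides consent and enrollment in the study", and gives an attribution rule: "Researchers will evaluate the connection between an event and the exercise intensity of the study protocol, based on a temporal relationship". It defines an adverse event as "any unfavorable functional occurrence in an individual consistently linked to exercise intensity".

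The Trial design section says that participants "will be submitted to a single session of each one of the following modalities of aquatic physiotherapy", and that between them "a minimum of a 15-day wash-out period will be respected". The Outcomes section states that before and after each intervention "all participants will have the following parameters evaluated: concentration of MMP-3 and GPx, pain, edema, flexibility, and self-perception of the general well-being". The Interventions section limits the reference group, which does the same programs, to biochemistry and the self-perception questionnaire.

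The Introduction hopes that the work will help to "prevent symptom exacerbation, minimize adverse effects, and provide greater therapeutic safety".

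**The concern.** Timing of harm surveillance is not left open here. The article fixes it at two looks, the later one at 24 hours. Participants then go at least two weeks before the next session, and no contact, diary or question about that interval is described.

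A flare that begins on day 3 and has gone by the next session falls between the looks. So does anything late after the third session, which has no following T0. At stake is how complete the safety record is in a trial meant to inform which intensity can be prescribed safely. The Monitoring section also declines a monitoring committee and auditing, so the Harms paragraph is the only systematic safety capture that the article describes.

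**Working it through.** The plan gives no figure to reproduce on this point. The check compares the time windows and then follows a late flare through each described route of capture.

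**Inputs**
- Last scheduled look for the named harms: 24 hours, that is day 1 (Monitoring, Harms).
- Minimum interval between sessions: 15 days (Trial design).
- Sessions per participant: 3, one of each program (Trial design).
- Participants: 15 (Trial design).
- Flare rate and time of onset: not given.

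**Windows**
- Share of the minimum interval reached by scheduled looks: 1/15 = 6.7%.
- Share with no described active check: 14/15 = 93.3%, or at least 14 days after each of the first two sessions (2 × 14 = 28 days per participant).
- After session 3 there is no later T0.

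**Routes by which a flare starting after 24 hours could be recorded**
1. *General adverse event recording.* This has a start, no stated end and no 24-hour cut-off, so a volunteered event would be recorded. No occasion for asking is described. The definition also requires a link to exercise intensity before something counts as an event, although that link is then to be assessed separately.
2. *The next T0.* Pain, edema and flexibility are measured before each session. A flare still present leaves a trace, but as a baseline value with no onset date. A resolved flare leaves none.
3. *The reference group.* It has no pain, edema or flexibility measures, so for these participants route 2 would not reveal even a persisting flare.
4. *The last period.* Route 2 does not exist. If the sequences are balanced (an assumption, since the article does not say), each program comes last for about 15/3 = 5 participants.

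**Illustration with assumed rates.** Let p be the chance that a participant flares after a given program and L the fraction of flares that start after 24 hours. The chance that at least one of 15 participants flares is 1 − (1 − p)^15. The chance that at least one flare has begun by the 24-hour look is 1 − (1 − p(1 − L))^15.

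| p | Any flare | L = 25% | L = 50% | L = 75% |
|---|---|---|---|---|
| 5% | 54% | 44% | 32% | 17% |
| 10% | 79% | 69% | 54% | 32% |
| 20% | 96% | 91% | 79% | 54% |

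For p = 10% and L = 50%: 1 − 0.95^15 = 54%, against 1 − 0.90^15 = 79%. The loss ranges from small to large depending on L, on which the documents are silent.

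**The case against.** The strongest reply is that short surveillance suits the question. The limitations paragraph of the Discussion states that the objective is acute effects. The safety sentence in the Introduction is a hope about later use, and the Statistical analysis section plans no comparison of adverse events between programs. The article may also condense a fuller harms procedure, and it lists a data collection form that is not at hand.

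Much of this stands, and it rules out several stronger readings that a reader might draw:
- *Late flares go uncounted.* Not supported: adverse event recording has no 24-hour limit, and T0 measures would show a persisting flare in the experimental group.
- *Late flares cannot be tied to a program.* Not supported: each period holds one session of one program, and the Harms paragraph judges the link by timing. A dated event can be assigned to the preceding program.
- *The plan itself treats effects as lasting 15 days.* Not supported: the article gives no rationale for the wash-out length, and a wash-out is a margin against carry-over.
- *The gap biases the comparison towards no difference in harm.* Not shown: that needs delayed flares to occur and to differ by intensity, and no rate is given.

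The reply does not remove the narrower point. The article states a two-look schedule, which is more than silence, and that schedule leaves later flares to spontaneous report. The temporal rule also needs an onset date, and no described procedure collects one.

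**Conclusion.** The point holds as a gap in active ascertainment. Flares that start after 24 hours and resolve before the next T0 are not described as actively sought and may be under-counted. Persisting flares appear only as undated T0 values in the experimental group and not at all in the reference group. After the third session nothing further is scheduled.

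The measurable size is 14 of at least 15 days (93.3%) without a described check. This is not an estimate of events missed, because risk after exercise need not be uniform over the interval. The direction and size of any bias are unknown. The conclusion assumes that no active check is specified in documents not shown. It is a worthwhile, cheap improvement and does not invalidate the design.

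Separately, the Outcomes section restricts the 24-hour follow-up to biochemistry and self-perception, whereas the Harms paragraph promises examination for pain, inflammation and flexibility then. The two must be reconciled. If the Outcomes section governs, the named harms are not examined even at 24 hours.

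**What to change.** In the Harms paragraph:
- Define the harm window for each program as running from the session to the next session's T0.
- At the T0 of the second and third sessions, in both groups, ask about and record knee worsening, other events and care sought since the previous session, with onset and end dates.
- Attribute these by date to the preceding program, and flag any event still open at T0 so that the affected baseline can be identified in the analysis.
- For the third session, add one brief closing contact after an interval that the sponsor chooses, or state in the report that late harms of the last program were not actively sought.
- Reconcile the Outcomes and Monitoring sections on what is examined at 24 hours.

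For 15 participants the cost is 15 × 2 = 30 short question sets at visits already planned, plus 15 closing contacts if that option is taken. The reference group adds to this, but the article does not state its size. The downside is recall over about two weeks. Recruitment had not begun according to the Study status entry, so the change can apply from the first participant.

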### Ethics and dissemination

*Ethics approval and consent*

This research was approved by the Research Ethics Committee of Federal University of Health Sciences in Porto Alegre in 15/05/2020 founder the number 4.030.865 and Presentation Certified for Ethical Appreciation (CAAE) number 29447220.5.0000.5345. Patients will be invited to participate in the study voluntarily, and they must consent to their participation by formalizing the Free and Informed Written Consent according to established by resolution number 466 from the National Health Council.
^
48
^ The study is planned to take place at University Feevale, and ethical approval has been obtained from the Research Ethics Committee of the Federal University of Health Sciences in Porto Alegre. This choice of institution for ethical approval is due to a strategic partnership between the two universities for this research endeavour. The partnership was established because our research advisor is affiliated with the Department of Physical Therapy at the Federal University of Health Sciences, making this institution the natural choice for ethical oversight. This partnership ensures that both institutions are jointly responsible for the successful execution of the study and ethical compliance is maintained throughout. The University Feevale is a co-participating institution in the research and, as such, declares its compliance with Resolution CNS 466/2012, which pertains to Brazilian regulations for research involving human subjects.

*Protocol amendments*

While the prescribed protocol has been deemed safe, having undergone pilot interventions within the aquatic physiotherapy department of the university, any modifications that might impact the study’s execution will necessitate renewed consideration by the Ethics Committee.

*Confidentiality*

Participant study data will not be disclosed beyond the study without explicit written consent from the participants. This confidentiality is upheld through the previously approved Informed Consent Form.

*Access to data*

Sole access to the datasets will be granted to the Principal Researcher. Project data shall be securely stored within password-protected files. To ensure privacy, data shared with project team members will be stripped of any participant-identifying information.

*Ancillary and post-trial care*

The responsible researcher will promptly provide comprehensive support to research participants concerning potential complications and resulting implications. Similarly, considering the research’s conduct within an accredited aquatic physiotherapy service, the service will consistently uphold any requisite therapeutic follow-ups after the study.

*Dissemination*

The study will be disseminated in printed and digital media, on the researcher, university, and the academic directory of health courses social media, in the Medicine Leagues, and on institutional pages.

**Study status**

Not yet recruiting.

## Discussion

The protocol presented in this study demonstrates different modalities of a single intervention in aquatic physiotherapy considering low, medium, and high-intensities strategies and aims to evaluate their effects on biochemical behavior in pain, edema, and flexibility in patients with knee osteoarthritis.

The proposal of low-intensity intervention consists of movements that involve the upper and lower limbs and trunk and are highly recognized by their relaxation capacity, potentiated by the interactions between their practitioners and the properties of the liquid environment.
^
49
^ This strategy has proven to be an effective method in the improvement of the symptoms and quality of life of patients diagnosed with Fibromyalgia,
^
50
^ reducing the risk of falls in older adults and producing an improvement in gait.
^
51
^ Regarding knee osteoarthrosis, this treatment option demonstrated to be capable of positively interfering in the reduction of pain, stiffness, functionality, and the quality of life because of the thermal effects of the immersion and the interactions provided by the physical property of water associated with slow and relaxing movements.
^
43
^

The aquatic physiotherapy intervention, when implemented, must take into consideration the body constitution, the speed of the movement, and the depth of the water as fundamental determinants to compose the intensity of the programmed exercise. Moving a segment in water requires more effort than moving oneself on the ground. The reduction of body weight experienced with the immersion also reduces the load on articulations affected by osteoarthritis and allows the performance of the closed-chain functional exercises that might otherwise be very difficult to perform on land. In the same way, the water turbulence might be used as a method to increase the resistance, and the percentage of body weight carried by the lower limbs can be decreased or increased directly proportional to the immersion depth.
^
22
^

Therefore, using the physical principles of the water becomes a great ally when aiming to treat individuals in this environment. For example, floating can reduce pain in patients with osteoarthritis since immersion is directly related to the reduction of body weight. In this situation, decreasing load means reducing articular pain, allowing a patient with osteoarthritis to perform exercises where the body weight variations can be constituted as an important therapeutic strategy for performing functional exercises, which is hard to adapt to the ground.
^
24
^

The hydrostatic pressure is directly related to the immersion depth, which has a positive effect on venous blood return and reduction of edema.
^
26
^ Water can retain the temperature and is an important thermal conductor capable of transferring thermal variations to the immersed body. The aquatic physiotherapy programs performed at temperatures ranging from 33.5-35.5°C allow heat transfer to the segments in contact with water and pain relief.
^
52
^

Widely used, aquatic exercises provide positive results in joint mobility and muscle strength because, with the immersion, the impulsion force provided by floating reduces the weight of body segments in a directly proportional way to the volume of displaced water, and this condition favors the movement of individuals with muscle weakness.
^
53
^

Benefits such as an improvement of functionality, muscle strength, and quality of life are observed in patients with osteoarthritis and other skeletal muscle disorders after aquatic physiotherapy.
^
52
^ The implementation of treatment programs for knee osteoarthritis can also be planned from high-intensity exercises. This option of intervention is from adjustments in variables such as the increase in the period of training (weeks, months), frequency (days, weeks), session (minutes), or the amount of effort generated with the activity (heart rate, effort). This way, the composition of a program of high-intensity
*versus* low-intensity must take into consideration the performance of the same program of exercises or physical activity in both groups, however, with different intensities.
^
47
^

Considering that this protocol aims to explore the effects of different programs of aquatic physiotherapy, to increment the work imposed during the performance of each one of the programs, the variables time, resistance, and movement speed will be proportionally modified. High-intensity training is known to bring benefits by contributing to functional performance and reducing the risk of falls for patients with knee osteoarthritis, and when performed in an aquatic environment, producing less load than when performed on the ground.
^
54
^ Lower articular load and lower generation of pain are clearly observed in squat exercises performed in a swimming pool, which indicates the great therapeutic potential of aquatic physiotherapy for patients with this condition.
^
55
^

The swimming pool walk is an important component for the improvement of the aerobic capacity of patients with osteoarthritis. This activity in the liquid environment requires speeds 30% lower than on the ground, while accelerating walks demand an increase of work of the cardiovascular system and require more strength for its execution. Walking with water at a depth corresponding to the xiphoid appendix reduces the articular overload, however, the increase in the speed can selectively recruit the hip extensor musculature, while walking backward reduces the patellofemoral compression, relieving compressive loads on this joint.
^
56
^ Running in the water is also considered an important intervention strategy for patients with osteoarthritis, as it demands a varied combination of exercises involving upper and lower limbs.
^
56
^
^–^
^
58
^

Nevertheless, although the improvement of functional variables in patients with osteoarthritis is widely unknown, the understanding of molecular mechanisms and their effects on articular cartilage are still scarcely explored. The effects of an aquatic exercise program on degenerative modifications of articular cartilage in an experimental animal model of knee osteoarthritis evidenced alterations in MMPs concentrations
^
26
^ and demonstrated that aquatic physiotherapy was able to produce more integrity and orientation of collagen fibers.
^
27
^ In this context, the analysis of biochemical markers constitutes a relevant topic of study by evaluating the effects of different modalities of aquatic physiotherapy on the functional and biochemical behavior of patients with knee osteoarthritis and becomes more relevant when seeking understanding and answers obtained in different work intensity programs on articular cartilage. The expected results with one single session will be indicative for future longitudinal studies based on assertive intervention proposals regarding protocols with lower production of biochemical agents responsible for collagen degradation.

Finally, immersion-based physiotherapeutic treatment can prevent cartilage degeneration, inhibit inflammation, and prevent subchondral bone loss, as the presented evidence indicates that this modality can improve pain, stiffness, joint dysfunction, and muscle weakness in patients with knee osteoarthritis. Similarly, various treatment options are characterized by exercises of different intensities, such as aerobic exercises or strength training.
^
59
^ Thus, the expected results in this protocol may support future longitudinal studies, contributing to assertive intervention proposals and constituting protocols aimed at reducing the production of biochemical agents responsible for collagen degradation.

The authors believe that this study, while providing important information, has some limitations. First, biomarkers considered important for understanding knee joint metabolism will be used. However, the inclusion of Cartilage Oligomeric Matrix Protein (COMP), a protein found in the extracellular matrix of cartilage, tendons, and other connective tissues, as well as other metalloproteinases and the analysis of inflammatory cytokines such as IL-1, IL-6, IL-8, and TNF-α, could offer a more detailed analysis of the acute effects of aquatic therapy on metabolism across all joint tissues. Second, the systemic response of the markers will be assessed. The authors are aware that analyzing intra-articular samples could provide information about this microenvironment; however, extracting intracavitary knee samples poses a significant challenge for implementing exercise in immersion, as sample collection involves invasive procedures in the joint cavity, which could contraindicate immersion immediately after collection. Third, interlaboratory variability and slight variations in existing study protocols can make it extremely difficult to compare results from different interventions to better understand the role of exercise characteristics and their impact on serum concentrations of soluble markers in this protocol. Fourth, the objective is to analyze the acute effects of different aquatic therapy protocols, but it is understood that future longitudinal studies, supported by the results from the implementation of this protocol, could provide better information on long-term interventions.

